##### Moderate intensity intervention

The same 12-week interactive self-study course is available as in the high-intensity arm with all features, except for the webinars. Again, only the first module is activated in the self-study course at the beginning. In this arm, however, participants can unlock the following modules independently by completing the previous one. They therefore determine the learning rhythm completely on their own. The participants are advised several times during the course that the modules have been designed in such a way that the optimum processing time for each module is about 1 week. Static information material is equally provided as in the high-intensity arm. Since participants are not assigned to a personal coach without the webinars, they direct their inquiries to a coach-supervisor via the chat function to ask for advice. Requests on psychological topics are answered by the psychological head investigator, while medical questions are answered by a physician of the study team.

The coach-supervisor also leads the quality assurance and supervision sessions in the high-intensity intervention. For specific questions, the coach-supervisor seeks the advice of a qualified specialist from the study team (physician, physiotherapist, etc.).

##### Control

Only content that participants could have found without professional guidance should be available here. For ethical reasons, a quality check was carried out to ensure that all information provided is basically correct and does not conflict with the principles of evidence-based treatment. Participants therefore receive 12-week access to a reduced version of the self-study course containing only the static information materials. All interactive, responsive, or didactically optimized content is not offered. At the beginning, again only module 1 is unlocked and the activation of further modules is equivalent to the moderate intensity arm. The chat function, coach support, or other didactic interaction are not available to participants in this arm.

#### Criteria for discontinuing or modifying allocated interventions {11b}

No changes to the assigned interventions are intended. However, all exercises shown in the program are voluntary and can be done or skipped by the participants individually. Thus, less intervention components deemed by the participant to be less beneficial can be excluded individually.

The attending GP may exclude participants from further participation at any time for medical reasons. The assessment of reasons (e.g., worsening disease) is the exclusive responsibility of the GP.

Participants themselves can terminate their participation at any time by revoking their consent.

Any of the following situations during the study period will also lead to discontinuation:Hospitalization due to COVID-19 or post-COVID-19-disease.Referral to long-term specialist outpatient treatment due to COVID-19 or post-COVID-19 disease.

#### Strategies to improve adherence to interventions {11c}

For monitoring adherence and participation indices, the LMS provides a dashboard that can only be accessed by the study management team. It allows real-time monitoring of participation numbers and group distributions.

Several measures have been taken to increase adherence.

##### Starter kits

All participants receive a starter package as a gift upon joining the study. The package consists of branded carrier bags containing a ball pen, a keychain, and a notebook that participants can use to work on exercises during the program.

##### Reminder emails

Participants receive a reminder email at defined events within the patient journey, in case of inactivity or if they miss a checkpoint in the process. Specifically:In case of an incomplete registration process.Appointment reminders on webinar days.In case of inactivity (7 days without interaction in the LMS).When there is a new system message or chat message in the LMS inbox.In case of non-response to a mandatory questionnaire.

##### Incentives

Among all participants who have completed 80% or more of the evaluation measures, €25 e-gift vouchers will be raffled (about 1 in 3 chances).

##### Feedback on health determinants

There are various health trackers within the LMS platform that participants can use to monitor their progress throughout the program. In addition, after each completion of the short weekly symptom questionnaire, participants receive direct feedback as a graphical visualization of their scores on multiple determinants of health in comparison to the previous week. This feature is also available to the control group and exceeds what participants would find on other websites or on the Internet.

#### Relevant concomitant care permitted or prohibited during the trial {11d}

All concomitant treatments or interventions that match the exclusion criteria described in {10} are prohibited during the trial. The same applies to interventions directly caused by any of the exclusion criteria, e.g., psychiatric therapy due to a current psychiatric illness. Other treatments are accordingly allowed.

#### Provisions for post-trial care {30}

Follow-up care after the trial is guaranteed as follows:

By involving the treating GP as the study physician, follow-up treatment is ensured via the usual care with full transparency about the interventions carried out.

A trial participant insurance policy was contracted for all participants.

### Outcomes {12}

#### Primary outcome

Primary outcome is the cumulative sum of sick leave days in patients during the period from enrollment to 6-month follow-up. We compare the high-intensity intervention versus moderate-intensity intervention versus control group. In Germany, every employee requires a medical sick leave certificate. The medical sick leave certificate entitles to 6 weeks of continuous payment of the salary by the employer. Thereafter, for additional 180 days, the statutory health insurance provides 80% of the net salary. Law mandates that employers offer employees with sick leave of longer than 6-week duration the opportunity to participate in a structured employment reintegration program (BEM). In such programs, patients are attempted to be reintegrated into their former jobs in agreement with the occupational health physician, the employer, and the employees’ representative board. The usual process is to gradually increase the weekly job hours and job requirements expressed as a percentage of full employment. Therefore, if a patient takes part in such a program, the sum of days that the participant has spent within an integration percentage stage is used as the primary outcome instead (e.g., 10 working days at 50% equals 5 days on full sick leave). In both cases—sick leave days and reintegration days—the data is reported directly to the study management by treating GPs via their health care networks at once at the end of the trial.

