### Objectives {7}

The primary aim of this study is to determine whether two different intensities of a 12-week online-based tailored educational digital intervention program for Long COVID patients (and currently infected prevention patients) provide a larger benefit than well-presented digital information alone on the primary endpoint days of sick leave accumulated over a 6-month period. If patients are in a structured employment reintegration program, reintegration days and employment percentage (hours compared to full time) will be used.

The secondary objectives are change in symptom severity or frequency, quality of life, work ability and work productivity, participation and dropout rates, and the usage behavior of the LMS content during the 6-month observation period.

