### Data collection and management

#### Plans for assessment and collection of outcomes {18a}

##### Primary outcome

GPs document sick leave days and BEM days in patient records as part of their normal work outside the study. At the end of the trial, the GP totals these days per study participant she enrolled for a period of 6 months counting from the day of registration in the LMS. This registration is defined as the start of the intervention. The GP then writes the accumulated days into a pseudonymized list of her patients and transmits this file to the study center via an end-to-end encrypted virtual data safe access. This simple procedure reduces the workload for GPs and eliminates the need for special instruction.

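### The primary endpoint as worded drops full sick-leave days for participants who enter a reintegration programme, and other sections read differently; the rule must be settled as a sum

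*Protocol article*

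**What the plan says.** Outcomes {12}, Primary outcome, opens with a plain count: "Primary outcome is the cumulative sum of sick leave days in patients during the period from enrollment to 6-month follow-up". It then explains that the law requires that "employers offer employees with sick leave of longer than 6-week duration the opportunity to participate in a structured employment reintegration program", and that for a patient in such a programme "the sum of days that the participant has spent within an integration percentage stage is used as the primary outcome instead". The only worked conversion is that "10 working days at 50% equals 5 days on full sick leave". The section closes by treating sick-leave days and reintegration days as two cases, both reported by the GP at the end of the trial.

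Objectives {7} says that for patients in a programme "reintegration days and employment percentage (hours compared to full time) will be used". It does not say whether these are added to sick-leave days or take their place.

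Plans for assessment and collection of outcomes {18a}, Primary outcome, says that "GPs document sick leave days and BEM days in patient records as part of their normal work outside the study", and that at the end of the trial the GP totals them over 6 months from LMS registration. "The GP then writes the accumulated days into a pseudonymized list of her patients". No section states that a BEM participant's full sick-leave days are kept and added to the converted days.

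**The concern.** The word *instead* in Outcomes {12} is a replacement rule. BEM is offered after more than 6 weeks of sick leave, so the rule applies to people who have already had a long absence. Any of that absence falling inside the window is removed from their score. The outcome then need not rise with time off work: someone with a long absence and a short programme can score below someone who was off for a few weeks.

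This can reach the treatment comparison. BEM entry during follow-up happens after randomisation and depends on how long the participant has been off. An arm with fewer long absences may have fewer people rescored, and the contrast then mixes the effect on absence with the effect of the scoring rule.

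The collection section makes matters less certain, because totalling both kinds of day suggests a sum. If each GP resolves the wording alone, different rules may be applied within one trial.

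**Working it through.** **Inputs from the protocol article.** Sample size {14}: control mean 30 days, SD 10, 180 days of follow-up; reductions of 4 days (high intensity) and 1 day (moderate), giving means 30, 29 and 26; power 80%, type 1 error 5%, dropout 25%. Outcomes {12}: BEM offered after more than 6 weeks, taken as 42 days; the 50% conversion example.

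**Assumptions, because the document gives no figures.** BEM uptake, equivalent days per programme, a gamma shape for sick-leave days with SD 10 in both arms, equal uptake in the arms, and all leave falling inside the window.

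**1. The plan's own figure.** For a three-group ANOVA, noncentrality = n × Σ(mean − grand mean)² / SD². The grand mean is 28.33 and the sum of squares is 2.78 + 0.44 + 5.44 = 8.67. With n = 113 this is 113 × 8.67 / 100 = 9.79, and power is 0.803. Then 113 / 0.75 = 150.7, rounded up to 151, as stated. The 4-day difference at SD 10 is therefore a fair yardstick.

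**2. Individual scores.** Let F be full sick-leave days in the window, d the days in a stage and e the employment percentage. Replacement scores Σ d(1 − e); addition scores F + Σ d(1 − e).

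| Full days | Programme | Replaced | Added |
|---|---|---|---|
| 30 | none | 30 | 30 |
| 45 | 10 working days at 50% | 5 | 50 |
| 60 | 20 working days at 50% | 10 | 70 |
| 60 | 20 working days each at 25%, 50%, 75% | 15 + 10 + 5 = 30 | 90 |

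A score of 10 lies (30 − 10) / 10 = 2 SD below the planned control mean. The reversal fades with programme length: at 50%, 60 working days score 30 and 86 score 43.

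**3. Arm contrast.** Let q be the share above 42 days, m their mean days, u the uptake among them and w the equivalent days per programme. Replacement lowers an arm mean by u × q × (m − w); addition raises it by u × q × w. The gamma model, in whole days, gives q = 0.112, m = 49.1 for control and q = 0.065, m = 49.0 for high intensity. With w = 10:

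- Replacement, u = 1: losses 0.112 × 39.1 = 4.4 and 0.065 × 39.0 = 2.5. They differ by about 1.8, so 4.0 becomes about 2.2 days.
- Replacement, u = 0.25: 0.25 × 1.8 = 0.5, so 4.0 becomes about 3.5 days.
- Addition: 10 × (0.112 − 0.065) = 0.5 at u = 1, giving about 4.5 days; at u = 0.25, about 4.1 days.

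A simulation of 400,000 per arm agrees: 2.17 and 3.52 under replacement, 4.49 and 4.10 under addition. For uptake of 25% to 100% and 5 to 20 equivalent days, the replaced contrast runs from 1.9 to 3.6 days. Approximate pairwise power at 113 per arm is 0.31 to 0.82 under replacement and 0.75 to 0.84 under addition.

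The direction depends on equal uptake. With u = 0.25 in control and 0.50 in high intensity, the losses are 0.25 × 4.4 = 1.1 and 0.50 × 2.5 = 1.3, and the contrast rises slightly, to about 4.2 days.

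**4. The conversion.** At 50% the share worked equals the share absent, so the example cannot show which is the weight; 10 days at 25% employment give 2.5 or 7.5. It also counts working days, and no unit is stated for plain sick-leave days. Two weeks at 50% are 10 × 0.5 = 5 working days or 14 × 0.5 = 7 calendar days.

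**The case against.** The strongest reply is that addition was meant all along. The outcome opens as a cumulative sum, the example turns stage days into full-sick-leave equivalents (the natural step before adding them), and the collection section has the GP total both kinds of day. This has weight: the document does not establish a settled rule that discards days. It does not remove the problem, because the one sentence that defines the outcome for these participants says replacement.

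Several stronger readings are tempting and are not supported:

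- *The longest-sick are scored as among the least sick.* Only BEM entrants are affected. BEM is an offer, and people who stay on full leave keep their whole count. Long programmes can score at or above the planned mean.
- *All the qualifying leave is lost.* Counting starts at registration, and treatment-path patients were infected at least 3 months earlier. The 6 weeks may precede the window and would then be excluded under any definition.
- *The contrast shifts by 3 days.* That needs, for example, 15% of control and 10% of high-intensity participants to enter BEM after 60 in-window days (0.15 × 60 − 0.10 × 60 = 3). These shares have no source. At mean 30 and SD 10, 60 days is 3 SD out, and the gamma model puts about 0.7% of controls there.
- *The study centre cannot apply the weighting.* The collection section does not say that percentages are left out, and the GP could convert while totalling. A condensed article may also omit the reporting template.
- *Planning used calendar days.* The 180 days describe follow-up and do not fix the unit of an illness day.

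On the weight, the context makes the share not worked the only sensible choice, so that part is a matter of wording.

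**Conclusion.** The point holds in a limited form. The primary endpoint is either wrong as literally written or open to two incompatible readings, and Objectives {7}, Outcomes {12} and the collection section {18a} must be reconciled.

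For individuals the consequence is certain under the literal rule: BEM entrants lose their in-window full sick-leave days, and a long absence with a short programme can score below a shorter plain absence. For the arm contrast, distortion is possible but its size is unknown. The shrinkage to about 3.5 or 2.2 days rests on assumed uptake (25% or 100% of those above 42 days), 10 equivalent days, a gamma shape, equal uptake and leave inside the window. It shows sensitivity and is not a forecast. That treatment changes BEM entry is plausible but not shown.

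It still needs settling before the GP lists are called in. It concerns the primary outcome, and Who will be blinded {17a} says that study management and analysts are generally not blinded, so a choice made after the data arrive would be open to challenge.

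**What to change.** Define the primary outcome as full sick-leave days within the window plus the sum over BEM stages of days in stage × (1 − employment percentage). In Outcomes {12}, replace *instead* with wording that the converted days count in addition to the full sick-leave days, and align Objectives {7} and the collection section with it. State one day unit for both components, and add an example at a percentage other than 50% so that the direction of the weight is clear.

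Have the GP list carry full sick-leave days and days at each BEM percentage in separate columns, with the conversion done centrally by one rule.

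The cost is wording in three sections and a few columns in a list sent once at the end of the trial. GPs already record both kinds of day, so nothing already collected is lost. The sample size needs no change on this account.

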#### Secondary outcomes

Secondary outcomes are change in quality of life, work ability, work productivity, and symptom occurrence and severity. These will be collected via questionnaires using patient-reported outcome measures (PROMs, see below). Participants complete comprehensive surveys at enrolment (T0 questionnaire, approx. 20 minutes completion time, baseline values), after finishing the 12 modules of the intervention period (T2 questionnaire, approx. 10-min completion time, after 3 months) and as mid-term follow-up 6 months after enrolment (T3 questionnaire, approx. 10-min completion time). In addition, a short questionnaire is collected weekly (T1 questionnaire, details see below). T0, T2, and T3 assess the following dimensions of health: health-related quality of life (mental and physical), physical complaints, depression, anxiety, burnout, pain, social support, physical fitness, shortness of breath, sleep quality, and work ability. Current medication, vaccination status, concentration issues, and individual COVID-related medical history as possible influencing parameters are collected at T0. The T0 questionnaire also obtains indicator scores for disease courses or symptoms which require adjusted specific module components. The disease courses or symptoms considered are post-exertional malaise (PEM), myalgic encephalomyelitis/chronic fatigue syndrome (ME/CFS), and orthostatic intolerance (OI). If required on the basis of the specific score of a participant, the LMS content is automatically adapted for high-intensity or moderate-intensity physical exercises within the intervention.

Once weekly during the intervention period, participants complete a short questionnaire (T1.1–T1.12) of 5-min completion time. This questionnaire offers short questions on current symptoms, well-being, and again work ability. As a direct feedback, participants receive a visualization in the form of a radar chart comparing their current values to the data of the previous week.

Furthermore, participants of the high-intensity and moderate-intensity groups have the possibility to report on how they are feeling in terms of energy level, overall health, pain, mood, number of enjoyable activities, and exercise level in visual analog scales via the LMS as often as they like during the intervention period. This tracker data is presented to the participants as a progress graph line chart.

The high rate of sick leave days in Long COVID patients could be directly related to the variety and severity of symptoms that patients experience [12, 29]. An improved ability to work could therefore be seen as an indicator for an improvement in the activities of daily life and the symptoms.

Further secondary outcomes are participation and dropout rates, including the exact dropout points during the process (directly derived from the user data of the LMS). Finally, we obtain meta-data on the use of resources, particularly the overall usage statistics of the LMS (e.g., which pages and multimedia content were accessed and how often, which bookmarks were set, which exercises were completed repeatedly and how often, how many reminder mails had to be sent and when).

At the end of the trial, all the secondary outcomes data described is exported at once by the provider of the LMS and sent to the study data management after appropriate pseudonymization.

Possible side effects are also recorded as secondary outcomes. These are reported directly and anonymously by the respective treating GP to the study management team. These reports include the methods used for diagnosis of side effects.

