#### Concealment mechanism {16b}

The allocation table is stored in the LMS and is queried by an automated script during the registration process. The stratification variables are known, because they are collected via the T0 questionnaire which takes place before the randomization process. In concrete terms, this means that after participants have registered in the LMS with their code, they complete the T0 questionnaire and are then automatically assigned to an intervention group. Thus, additional measures to establish the allocation sequence are not necessary, as no active action is required due to the automatism. Likewise, no measures to conceal the sequence are necessary due to the automation.

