### Assignment of interventions: blinding

#### Who will be blinded {17a}

Participants themselves are blinded. They only receive the information that they have been assigned to an intervention group called “A,” “B,” or “C.” The participants do not know which measures are possible. They also do not know which intervention portfolio is associated with which letter. GPs are blinded in the way that they are not told which group a patient has been allocated to.

The study management and data analysts themselves are generally not blinded. However, they do not have direct access to participant data and participants during the trial period, and the evaluation is done on aggregated data once the study is completed.

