#### Confidentiality {27}

##### General data protection regulations

Throughout the entire project, the data protection regulations according to the GDPR are strictly adhered to and controlled. An accompanying assessment by the responsible department for data protection has been carried out for all relevant aspects. For concrete details on individual measures, please refer to the comprehensive respective documents.

Nevertheless, special reference is made to the constant pseudonymization of patient data at all trial steps.

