##### Enrolment and accompanying care

All measures carried out by the GP are subject to medical confidentiality and the data protection standards according to which medical practices are obliged to work. GP keep the pseudonymization key in the patient record, as they are the only party usually holding unencrypted patient data.

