##### Data transfer

Any data transfer between stakeholders that includes the health data of participants will only be conducted in pseudonymized form. When data sets or outcome information is sent, this is done exclusively via end-to-end encrypted password-protected virtual data safe access.

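### Side effects are a secondary outcome, but GPs are to report them anonymously, which contradicts the protocol's own pseudonymization rule and, if followed, prevents analysis by arm

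*Protocol article*

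**What the plan says.** The Secondary outcomes text under Outcomes {12} gives side effects the status of an outcome: "Possible side effects are also recorded as secondary outcomes". It then states the route and form: "These are reported directly and anonymously by the respective treating GP to the study management team". The one item of content it names is diagnostic: "These reports include the methods used for diagnosis of side effects". No participant code is mentioned.

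The sections under Confidentiality {27} set a different rule. General data protection regulations says that "special reference is made to the constant pseudonymization of patient data at all trial steps". Data transfer is stricter still: "Any data transfer between stakeholders that includes the health data of participants will only be conducted in pseudonymized form". Enrolment and accompanying care adds that "GP keep the pseudonymization key in the patient record".

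Two further statements decide whether a report can be traced to an arm. Under Concealment mechanism {16b}: "The allocation table is stored in the LMS and is queried by an automated script during the registration process". Under Who will be blinded {17a}: "GPs are blinded in the way that they are not told which group a patient has been allocated to".

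Adverse event reporting and harms {22} makes the GP the first point of report, lets participants also report to any other party in the project, and leaves the reporting chain to contracts that are not shown.

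**The concern.** A secondary outcome in a three-arm randomized trial is useful only if each observation can be assigned to a randomized group. An anonymous report cannot be. It also cannot be assigned to a person, so two reports might be one participant twice or two participants once.

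Harms matter in this comparison. The two active arms contain exercises that the information-only arm lacks, and the platform adapts some of that content for participants with indications of post-exertional malaise, ME/CFS or orthostatic intolerance. The protocol thus accepts that the content may not suit everyone equally. No data monitoring committee and no audit are planned, so the side-effect data examined at the end of the trial carry most of the weight on this question. A link that is not recorded when the report is made cannot be restored by any later analysis plan.

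**Working it through.** No arithmetic applies. The point depends on data linkage and not on sample size, power or an event rate, and the document states no expected rate of side effects. The check sets the statements side by side.

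1. **What a by-arm analysis needs.** Each report needs either the arm or a participant code that can be matched to the allocation table. Counting participants with an event, as opposed to events, needs the code in any case.

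2. **Can the GP supply the arm?** No. Under {17a} the GP is not told it. This is sound design and does no damage by itself: a blinded GP can send a coded report and the study center can add the arm.

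3. **Can the report be matched to the allocation table?** The table sits in the learning platform ({16b}), so a match needs a participant code.
   - Outcome section taken literally: the report is anonymous, there is no code and no match. Events by arm and participants with events by arm are both unavailable.
   - Confidentiality section applied: the report is pseudonymized, the code is present and the match can be made. Both counts are available.

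   The two rules give opposite answers for the same report.

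4. **Is the word probably just loose?** The text points both ways. In favour of loose wording, the confidentiality rules are general and allow no exception. Against it, the paragraph immediately before the side-effect paragraph says that the other secondary outcomes are sent after pseudonymization, so the authors had the right term at hand. The LMS paragraph under Confidentiality {27} also treats the two terms as different states: health data are pseudonymized now and are to be fully anonymized later, when the research permits. A reader who knows that distinction would take the side-effect sentence at its word.

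5. **Do other data fill the gap?**
   - *The additional route in {22}.* It is not described as anonymous, but no participant code is mentioned either. It supplements the GP route. Without a code on both routes, an event told to the GP and also to another party cannot be recognized as one event. One natural channel, the chat with a coach or coach-supervisor, is not offered in the control arm, so this route may also pick up events unevenly.
   - *The platform questionnaires.* Symptoms, pain, breathlessness, mood, physical function and work ability are collected from participants in all arms and can be linked to the arm. They show worsening on the scales asked about. They are not side effects as diagnosed and reported by a GP.
   - *The health trackers.* They exist only in the two active arms and give no comparison with control.

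6. **Is a coded report feasible?** Yes. The GP holds the pseudonymization key. Under Plans for assessment and collection of outcomes {18a}, the same GP sends each patient's sick-leave total in a pseudonymized list through an encrypted data safe. Code and route both exist.

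**The case against.** The strongest reply is that everything hangs on one adverb. The protocol's general rules require pseudonymized transfer, the GP has the key, and the primary outcome already travels in that form, so the word may mean no more than that the patient's name is left off. The article also condenses a fuller protocol, the reporting chain is defined in contracts that cannot be seen, and adverse-event forms are details that an article may properly omit. The platform data would show worsening by arm in any event.

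Much of this stands. A reader might infer that harms can never be compared between arms in this trial. The document does not support that: a competing rule in the same text would preserve the link, a further reporting route exists, and symptom data by arm are collected. A reader might also infer that keeping GPs unaware of the arm causes the loss. It does not, because linkage can be made centrally.

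What does not fall away is the contradiction. The finding is not that a form or field list is missing. The article makes an explicit statement on how a declared outcome is collected, and that statement conflicts with an equally explicit rule elsewhere. Someone who follows the outcome section exactly would strip the code that the analysis needs.

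**Conclusion.** The point holds as an internal contradiction with a definite consequence. The outcome section has side effects reported anonymously, while the confidentiality section allows health data to be transferred only in pseudonymized form. If the first is followed as written, every GP side-effect report lacks a link to the randomized arm, and neither events nor participants with events can be tabulated by arm. If the second is followed, nothing is lost.

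The conclusion assumes that an anonymous report carries no participant code, which is the ordinary meaning and agrees with how the document separates the two terms elsewhere. It does not assume that reports have in fact been sent without a code; the document cannot show which practice was adopted. The loss is confined to side-effect reports. The primary outcome and the questionnaire outcomes are unaffected. It should be corrected, because reports already received without a code may not be recoverable.

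**What to change.** Reconcile the passages. In the side-effect sentence of Secondary outcomes, replace the word *anonymously* with wording to the effect that reports are made under the participant's study pseudonym. Use the code that the GP already holds and the encrypted route already used for the sick-leave list. Apply the same code to reports arriving by the additional route in Adverse event reporting and harms {22}, so that duplicates can be recognized. State that the study center adds the arm, that the GP remains unaware of it, and that events and participants with events will be reported by arm. If any reports have already been received without a code, ask the reporting GPs whether the code can still be supplied, and disclose the number that cannot be linked.

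The cost is modest but goes beyond changing a word. The sick-leave list is a single total per patient sent once at the end of the trial, whereas side effects need a short event-level form, with at least the code, the event, its date and its severity, and possibly different timing. No new code and no new secure channel are needed.
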